## Abstract

**Introduction:**

Cognitive behavioral therapy (CBT) is recognized as one of the most effective methods for reducing the risk of perinatal depression. However, the traditional face-to-face delivery format limits its accessibility. With the advent of digital technology, app-based CBT offers new possibilities, yet its preventive role in perinatal depression remains insufficiently explored. This study aims to determine if pregnant women using an app-based CBT program report reduced depressive and anxious symptoms compared to a control group.

**Methods:**

A two-arm parallel randomized controlled trial of 290 pregnant women will be conducted at Jintang County Maternity and Child Health Hospital in Chengdu, China. Eligible participants who consent to participate will be recruited at 20-24 weeks of gestation and randomly assigned to either the intervention group, which will complete an 8-week mobile app-based CBT program (CareMom), or a control group, which will receive an attention-matched 8-week relaxation training program, also delivered via a mobile app. Randomization will be performed using a computer-generated random number sequence. Primary outcomes include changes in scores on the Edinburgh Postnatal Depression Scale, the Patient Health Questionnaire-9 and the Generalized Anxiety Disorder 7-item from baseline to 6 weeks postpartum. Outcome analyses will be performed on both the intention-to-treat and per-protocol populations.

**Discussion:**

This trial evaluates an app-based CBT program for reducing the risk of perinatal depression. Improved maternal mental health not only benefits the mothers themselves but also may facilitate more optimal parenting behaviors, which could exert a positive influence on the cognitive, emotional, and behavioral development of the infant.

**Clinical Trial Registration:**

https://clinicaltrials.gov/study/NCT06672432, identifier NCT06672432.

## Introduction

1

The perinatal period represents a critical transition into motherhood, marked by inevitable social, psychological, and hormonal changes that increase susceptibility to mental health disorders such as perinatal depression (1). According to the Diagnostic and Statistical Manual of Mental Disorders Fifth Edition (2), perinatal depression includes major depressive episodes occurring during pregnancy (antenatal depression) or within four weeks postpartum (postpartum depression). However, given that many depressive episodes tend to emerge beyond four weeks after delivery, postpartum depression is typically defined as the presence of depressive symptoms occurring up to 12 months after childbirth in the clinical and research settings (3).

Perinatal depression is common worldwide, with recent reviews estimating its prevalence rate to be between 12% and 25% (4, 5). In China, 16.3% of women were estimated to have symptoms or a diagnosis of perinatal depression (6). However, the treatment rate for major depressive episodes, particularly in psychiatric hospitals, was low at under 20% across the country (7). This low treatment rate may be due to several factors, including a lack of available mental health services, low socioeconomic status, and psychiatric stigma and discrimination (7). Perinatal depression, if left untreated, can lead to serious health consequences for both mother and offspring. Antenatal depression has been linked to delayed fetal development, preterm birth, low birthweight, poor maternal sleep, and an increased risk of postpartum depression (8). Mothers with postpartum depression often interact and communicate less with their infants, have lower rates of breastfeeding initiation and shorter breastfeeding duration, and their children may face delays in emotional, cognitive, and behavioral development (9, 10).

According to a recommendation statement of US Preventive Services Task Force (USPSTF), counseling interventions, such as cognitive behavioral therapy (CBT) and interpersonal therapy, are effective in preventing perinatal depression (11). CBT emphasizes that positive transformations in mood and behavior can be attained through the identification and management of negative thoughts, beliefs, and attitudes, as well as by enhancing positive experiences and activities. CBT provides people with strategies and tools to identify and modify maladaptive cognitive patterns, and behavioral activation.

CBT traditionally delivered in face-to-face formats, either individually or in group settings. With rapid advancement of internet and information technology, researchers have begun to assess the effectiveness of digital versions of CBT during the perinatal period. However, most studies have focused on its therapeutic applications rather than its preventive potential for antenatal and/or postpartum depression (12), leaving the preventive effects largely inconclusive. One large prevention study found that an internet-delivered CBT (iCBT) program, implemented during the second trimester, was ineffective in preventing new onset of perinatal depressive episodes. The authors suggested that iCBT might only be effective in preventing perinatal depression among pregnant women with subthreshold depressive symptoms (13). However, the preliminary evaluations of an app-based CBT program have shown promising reductions in depressive symptoms among postpartum Chinese mothers in the early postpartum period (14).

Given the importance of preventing perinatal depression starting in the antenatal period, we propose that implementing our CareMom program during the second trimester may effectively reduce subsequent depressive symptoms. Therefore, this randomized controlled trial (RCT) aims to evaluate the effectiveness of CareMom, an app-based CBT program, in reducing the risk of perinatal depression among Chinese mothers. We hypothesize that participants using CareMom will experience (1): lower depressive and anxious symptoms at the end of intervention, and (2) lower depressive and anxious symptoms at six weeks postpartum, compared to those receiving a relaxation course. The main objective of our study is to investigate postnatal depression, with the primary outcomes being the changes in depressive and anxious symptoms at six weeks postpartum.

## Methods and analysis

2

### Study design and setting

2.1

A two-arm, parallel RCT of 290 participants (145 in each arm) will be conducted at a public maternity hospital in Chengdu. Chengdu, the capital of Sichuan Province in southwest China, has a population of 15.9 million and a disposable annual income per capita of 47,948 RMB in 2022, exceeding the national average of 36,883 RMB. Eligible pregnant women who consent to participate will be recruited from the antenatal clinic of the maternity hospital between 20 and 24 weeks of gestation and will be randomly assigned to either the intervention or active control group using a computer-generated random number. Participants recruitment started in November 2024 and is expected to end in February 2025. We followed the Standard Protocol Items: Recommendations for Interventional Trials (SPIRIT) guidelines for developing our trial protocol (15, 16). The design of the RCT is summarized in **Figure 1**.

**Figure 1 f1:**
[figure not shown]
Flow diagram of the RCT.

### Participants

2.2

Pregnant women meeting the following inclusion criteria will be invited to participate in the study: (1) aged 18-45 years, (2) at 20-24 weeks of gestation, (3) at risk of depression but not experiencing severe depressive symptoms at recruitment, as indicated by an Edinburgh Postnatal Depression Scale (EPDS) score ranging from 5 and 12 (17), (4) own a smartphone, and (5) are able to independently engage with the program.

Pregnant women will be excluded from the study if they meet any of the following criteria: (1) have serious medical conditions or pregnancy complications that may affect their psychological condition, as determined by their medical doctor, (2) have a prior diagnosis of any mental disorders, (3) are currently or were recently (within the past six months) receiving any kinds of psychological services or treatments, (4) have a history of self-harm or suicide, (5) have any suicidal thoughts in the past 12 months, (6) experienced fetal deaths in the past 18 months.

### Recruitment and randomization

2.3

The participants will be recruited at the antenatal clinic. The researchers, who are obstetricians at the research hospital, will introduce the aims (i.e. to improve mothers’ mental health) and procedures of the study to potentially eligible women both verbally and through an information sheet. If a woman consents to participate, she will complete the consent and personal information forms. The personal information forms include the EPDS, along with questions addressing other eligibility criteria for the study, such as age, gestational week, pregnancy complications, history of mental disorders, etc. After reviewing the personal information, the researchers will then allocate eligible participants to either the intervention group (the CareMom group) or the active control group (the relaxation training group) using a computer-generated random number. The random numbers range from 0 to 1. If the number is greater than 0.5, the participant will be allocated to the CareMom group; otherwise, she will be allocated to the active control group.

### Data collection and measurements

2.4

We have developed online self-administered questionnaires using the survey platform WJX.CN (https://www.wjx.cn/), with corresponding QR codes generated for easy access. The schedule of measurements is present in **Table 1**.

**Table 1 T1:** Measurements to be taken at each point in trial.

	Study period			
	Enrolment	Allocation	Post-allocation	
		T_0_ (Day 0)	T_1_ (8 weeks)	T_2_ (6 weeks postpartum)
Informed consent	**×**			
Basic personal information (e.g. age, pregnancy complications, history of mental disorders)	**×**			
EPDS	**×**		**×**	**×**
Sociodemographic characteristics		**×**		
Reproductive history		**×**		
Lifestyle (cigarette smoking and alcohol drinking)		**×**		
Family history of mental disorders		**×**		
PHQ-9		**×**	**×**	**×**
GAD-7		**×**	**×**	**×**
CSQ-8			**×**	

EPDS, Edinburgh Postnatal Depression Scale; PHQ-9, Patient Health Questionnaire-9; GAD-7, Generalized Anxiety Disorder 7-item; CSQ-8, Client Satisfaction Questionnaire; **×**, measurements to be taken at this point.

Following randomization, all participants will be asked to scan a QR code to complete a structured baseline questionnaire, collecting data on sociodemographic characteristics (i.e. marital status, occupation, educational level, and family income), reproductive history, lifestyle factors (i.e. cigarette smoking and alcohol drinking), and family history of mental disorders. In addition to the EPDS which is collected at recruitment (18), we will also use the Patient Health Questionnaire-9 (PHQ-9) (19) and the Generalized Anxiety Disorder 7-item (GAD-7) (20) to evaluate participants’ depressive and anxiety symptoms at baseline. Trained nurses will be available for classification if needed.

The EPDS has been widely employed in antenatal and postnatal depression research to measure depressive symptoms over the past seven days (17). It consists of 10 items rated on a four-point scale from 0 to 3, with a maximum score of 30, where higher scores indicate more severe depressive symptoms. We will use the Chinese version of EPDS in this study (21). For Chinese women, EPDS scores above 9 suggest a high likelihood of depression (21, 22) and scores above 15 indicate severe depression (23).

The PHQ-9 is a widely used self-administered instrument for diagnosing and assessing the severity of depression. Patients rate the frequency of specific depressive symptoms experienced over the past two weeks on a four-point scale, ranging from “not at all” to “most days”. Total scores range from 0 to 27, with a score of 10 or greater being the most common cut-off for screening major depressive disorder (19). Studies conducted in mainland China have validated the reliability and validity of the Chinese version of the PHQ-9 in detecting major depression (24, 25).

The GAD-7 is a valid self-assessment tool used to measure anxiety symptoms over the past 14 days. It consists of seven items, each rated on a score from 0 to 3. The total score ranges from 0 to 21, with higher scores reflecting more severe anxiety symptoms. Scores between 5 and 9 suggest mild anxiety, and a score greater than 14 indicates severe anxiety (20). In our study, the Chinese version of GAD-7 is applied (26).

The depressive and anxiety symptoms will be measured at follow ups, with all participants asked to complete the EPDS, PHQ-9 and GAD-7 after the 8-week intervention period, and again at 6 weeks postpartum. The use of both EPDS and PHQ-9 allows for a more comprehensive assessment of depressive symptoms, as EPDS is specifically designed for perinatal populations and captures unique features such as anxiety and guilt, while PHQ-9 aligns with DSM-based diagnostic criteria, facilitating comparisons with broader clinical and research settings. This dual approach ensures a more nuanced evaluation of depression severity and symptom patterns in our study population. In addition, an acceptability survey will be administered to assess participant satisfaction level post-intervention. For participants who do not complete the project, their reasons for withdrawal will be gathered through a brief questionnaire.

In this study, we will use the Client Satisfaction Questionnaire (CSQ-8) to assess participant satisfaction with the intervention (27). The CSQ-8 is a widely used, standardized tool designed to measure client satisfaction with healthcare services and interventions. It consists of 8 items, each scored on a Likert scale, with higher scores indicating greater satisfaction. The questionnaire covers aspects such as perceived quality of service, the extent to which the service met participants’ needs, and their overall satisfaction with the experience.

All unfavorable or unintended events affecting participants in the study, such as physical discomfort, psychological distress, or any other negative experiences related to the intervention, will be recorded using a pre-specified adverse event questionnaire. Participants are encouraged to report any discomfort they experience, and all reported events will be documented and monitored throughout the study period.

Any serious adverse events will be promptly reported to the safety board of the trial, who will then evaluate the risks and provide recommendations to the research team on whether to continue, temporarily pause, or discontinue the trial due to any increased risk or significant adverse events. The safety board includes three experts specializing in clinical trial conduct, statistics, and mental health. The trial manager will compile a report detailing the number of adverse event notifications at each assessment period for review by the safety board.

### Interventions

2.5

Immediately after baseline data collection, all participants will be asked to scan a Quick Response (QR) code to open a mini program in the WeChat application.

The intervention program, CareMom, is a structured, 8-week digital intervention delivered through a WeChat mini-program in Chinese, developed by Shanghai Thoven Technology Co. Ltd., China, under the guidance of psychologists and psychiatrists. CareMom is designed to support perinatal mental health by providing daily challenges, educational content, and interactive exercises that target cognitive restructuring, behavioral activation, and worry management, key therapeutic components for alleviating symptoms of depression and anxiety.

The intervention is divided into daily tasks spread across eight weeks, with each day involving a variety of interactive elements such as videos, text-based content, guided reflections, and mental health check-ins. Upon logging into the system, participants are directed to a personalized dashboard page displaying their daily tasked need to complete (see **Figure 2**). If the user misses a daily challenge, she can complete that challenge in the later days. Each week has a distinct focus that progressively builds the user’s skills and understanding in managing emotional health. Tasks are designed to be short yet impactful, aiming to enhance engagement and adherence. **Table 2** describes the weekly focus of the 8-week intervention.

**Figure 2 f2:**
[figure not shown]
Screenshot of a daily task list within CareMom.

**Table 2 T2:** Description of the 8-week intervention program.

Week	Focus	Description
Week 1	Emotional Awareness	Participants engage in mood tracking, emotion identification, and gratitude journaling.
Week 2	Cognitive Patterns and Automatic Thoughts	Introduces participants to cognitive distortions and automatic thoughts.
Week 3	Core Beliefs and Cognitive Restructuring	Guides participants to identify negative core beliefs, challenge them, and replace them with positive ones.
Week 4	Anxiety Management Techniques	Focuses on anxiety management through techniques like progressive muscle relaxation, controlled breathing exercises, and understanding the physiological responses associated with anxiety.
Week 5	Advanced Cognitive Techniques for Worry	Builds on cognitive restructuring by addressing specific cognitive distortions like catastrophic thinking.
Week 6	Exposure to Feared Thoughts and Situations	Uses guided imagery and exposure-based exercises to help users confront distressing thoughts or worries gradually, with the aim of reducing avoidance behavior.
Week 7	Behavioral Activation for Positive Reinforcement	Introduces behavioral activation techniques, encouraging users to engage in enjoyable and purposeful activities.
Week 8	Consolidation and Long-Term Management	Users review and consolidate skills learned throughout the program, focusing on relapse prevention strategies and setting goals for maintaining emotional well-being beyond the intervention.

CareMom presents users with their daily tasks, which they are required to complete each day. These tasks typically include key components such as video-based psychoeducation (see **Figure 3**) and a mood checker (see **Figure 4**). Some tasks will automatically trigger interactive tools designed to help users complete specific tasks more effectively. For example, in Week 2, when users engage in cognitive restructuring, the Thought Challenger tool is triggered to assist them in identifying and challenging Automatic Negative Thoughts (see **Figure 5**). Similarly, during Week 3 on Anxiety Management Techniques, a worry-recording tool is activated to guide users in documenting and analyzing their worries (**Figure 6**).

**Figure 3 f3:**
[figure not shown]
Screenshot of a video for psychological education.

**Figure 4 f4:**
[figure not shown]
Screenshot of the mood checker tool.

**Figure 5 f5:**
[figure not shown]
Screenshot of the though challenger tool.

**Figure 6 f6:**
[figure not shown]
Screenshot of the worry recording tool.

Throughout the eight-week intervention, CareMom offers a range of additional tools tailored to different therapeutic goals. These include an activity list builder to support behavioral activation, a postpone worries tool for managing anxious thoughts, and tools for imaginal exposure and behavioral experiments to facilitate gradual desensitization and cognitive restructuring. By seamlessly integrating these tools into the daily tasks, CareMom ensures that users receive structured, hands-on guidance in applying intervention techniques to their daily lives.

In attention to the 8-week intervention program, participants in the intervention group will receive standard perinatal care throughout the study. This includes routine prenatal check-ups, postpartum nursing care, and scheduled postnatal visits, ensuring that all participants receive the essential healthcare services typically provided during the perinatal period.

### Matched attention control

2.6

The control group in this study will participate in an attention-matched, 8-week online relaxation training program delivered through a mobile application. This program is designed to mirror the structure and engagement level of the intervention group, providing participants with a similar amount of interaction and daily activities. Each day, participants in the control group will complete 1-2 daily tasks focused on relaxation techniques, such as breathing exercises, mindfulness meditation, and guided imagery. Each task is brief, approximately 3 minutes in duration, making it easy for participants to incorporate into their daily routine.

Similar to the intervention group, participants in the control group will receive a daily task list, where each day’s page presents relaxation-focused tasks. These tasks include breathing exercises, mindfulness meditation, and guided imagery, designed to promote relaxation and stress reduction. Each task is brief, approximately 3 minutes in duration, making it easy for participants to incorporate into their daily routine. CareMom also provides interactive tools tailored to each task. These tools assist users in completing their relaxation exercises more effectively. For example, CareMom includes a tool that guides users through their breathing exercises, ensuring they follow the technique correctly for maximum benefit (see **Figure 7**). Similar tools are integrated throughout the program to support various relaxation techniques, helping participants engage more deeply with the intervention.

**Figure 7 f7:**
[figure not shown]
Screenshot of the guided breathing tool.

User engagement and adherence in both the intervention and control groups are automatically tracked by the system, which records key metrics such as daily task completion, login frequency, module progression, and time spent on each activity. To minimize any potential adverse effects of breathing exercises (28), a cautionary statement was included in an appropriate location within the app: “Should you experience any discomfort during the breathing exercises, please stop immediately. If the discomfort persists, we recommend consulting your obstetrician.”

### Outcomes

2.7

Primary outcomes include changes in EPDS, PHQ-9 and GAD-7 scores from baseline (T_0_) to 6 weeks postpartum (T_2_).

The secondary outcomes include: (i) changes in EPDS, PHQ-9 and GAD-7 scores from baseline (T_0_) to post-intervention (T_1_), and (ii) comparisons of CSQ-8 results and the number of adverse events post-intervention (T_1_) between the intervention and control groups.

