### Sample size determination

2.9

In this study, to detect a medium effect size (d=0.37) for a two-tailed independent t-test at a significance level of 5% with a power of 80%, at least 115 participants are required for each group (29). Taking into account a loss to follow-up of 20% in our study, the total sample size required at baseline for the RCT is 290 (145 per group). It is assumed that approximately 30% of women will decline or be ineligible to participate; we plan to approach at least 415 pregnant women at the hospital antenatal clinic. G*Power software was used for the sample size calculation.

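### Three unranked primary outcomes, one power calculation tied to none of them and no success rule: the stated 5% and 80% hold together only if a single scale leads

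*Protocol article*

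**What the plan says.** Section 2.7 (Outcomes): "Primary outcomes include changes in EPDS, PHQ-9 and GAD-7 scores from baseline" (T0) to 6 weeks postpartum (T2). The abstract and the end of the Introduction give the same set. None of these places ranks the scales or names a lead.

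Section 2.9 (Sample size determination) plans "to detect a medium effect size (d=0.37) "for a two-tailed independent t-test at a significance level of 5% with a power of 80"%, and concludes that "at least 115 participants are required for each group". It then allows for 20% loss to follow-up and arrives at 290 in total, 145 per group. The effect size is standardised and is not attached to EPDS, PHQ-9 or GAD-7. This 5% is the only significance level in the article.

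Section 2.10 (Statistical analysis) describes random-effects models for the outcome variables, the analysis populations and the imputation. It gives no hierarchy, division of alpha or adjustment across the three scales, and no statement of which pattern of results makes the trial positive.

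**The concern.** The set of primary outcomes and the basis of the sample size are both protocol-level statements, and here they do not match: there are three primary outcomes and one test in the power calculation. A reader cannot tell what the 5% and the 80% refer to.

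The Discussion calls the trial definitive. Without a rule fixed in advance, the scale that carries the headline could be chosen after the results are known. Under an any-of-three reading the false-positive rate exceeds 5%; under an all-three reading the trial has less power than stated.

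**Working it through.** **Inputs from the protocol article.** Three primary outcomes (2.7); two-sided alpha 0.05, power 0.80, d = 0.37, 115 evaluable per group, 20% loss, 145 per group (2.9).

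**Assumptions not in the article.** Three equicorrelated normal test statistics with correlation r from 0 to 0.9; when the intervention works, d = 0.37 on every scale; 116 evaluable per group (145 × 0.8).

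**1. The plan's own figure.** Normal formula: n = 2(1.960 + 0.842)² / 0.37² = 114.7, so 115 per group. The exact t calculation gives 115.6, so 116 (power 79.8% at 115 and 80.1% at 116). With 20% loss: 115/0.8 = 143.75, so 144; 116/0.8 = 145. The stated 290 reproduces for one test at 5%.

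**2. Any one of three succeeds, each at an unadjusted 5%.** With independent scales the familywise error is 1 − 0.95³ = 14.3%. For correlated scales it is P(at least one |Z| > 1.96) under the null, by simulation with 4 million draws.

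**3. All three must succeed.** The familywise error is at most 5%. Each statistic has mean 0.37 × √(116/2) = 2.82, and joint power is P(all three Z > 1.96).

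**4. Any one of three succeeds, Bonferroni at 0.05/3.** The critical value is 2.394, and power is P(at least one Z > 2.394).

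| r | Familywise error, any of three, unadjusted | Power, all three at 5% | Power, at least one at 0.05/3 |
|---|---|---|---|
| 0 | 14.3% | 52% | 96% |
| 0.5 | 12.5% | 62% | 88% |
| 0.7 | 10.9% | 66% | 83% |
| 0.8 | 9.8% | 69% | 80% |
| 0.9 | 8.4% | 73% | 76% |

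In the last column the familywise error is 5% or less at every r. Power for one named scale at 0.05/3, with 116 per group, is 66%.

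**5. One named scale at 5%.** This is the calculation in step 1: error 5%, power 80%, 290 participants.

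**The case against.** The strongest reply is that the article condenses a fuller protocol, and that a multiplicity method commonly sits in the analysis plan, which is not shown. That stands as far as the method goes: its absence alone would not be a finding. It does not remove the mismatch between three primary outcomes in 2.7 and a single unassigned test in 2.9, because both are stated in the article.

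The reply also limits what can be claimed. Four stronger readings are tempting, and the article does not support them.

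- *The false-positive rate simply is above 5%.* No section says that each scale is tested at 5%, or that any one is enough. The 5% appears only in the sample size sentence. The hypothesis in the Introduction joins depressive and anxious symptoms and could be read as requiring both. The inflation is conditional, and its 14% end needs independence, which is implausible for self-report scales completed by the same woman.
- *The trial both inflates its error and loses power.* These belong to different success rules and cannot apply together. Under an unadjusted any-of-three rule power is not short: each scale has about 80% by itself.
- *GAD-7 contradicts the objective.* The Introduction does say "The main objective of our study is to investigate postnatal depression", but the same sentence goes on to include anxious symptoms among the primary outcomes. Anxiety is a declared aim.
- *Any correction across three scales forces a larger trial.* That is true only if 80% power is wanted for each scale separately. With an any-of-three rule at 0.05/3, the chance of at least one success at the planned size is about 80% or more for correlations up to 0.8.

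**Conclusion.** The point holds in conditional form. The sample size arithmetic is sound for one test, but the article does not say which test that is. If any one scale at an unadjusted 5% makes the trial positive, the familywise error is about 8% to 14% for correlations from 0.9 down to 0. If all three are required, joint power is about 52% to 73% for correlations from 0 to 0.9. The stated 5% and 80% apply together, as written, only when one scale leads.

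The figures rest on equal correlations, a common d of 0.37 and 116 evaluable women per group. The article gives no correlation, so a single figure within either range cannot be defended. Because the success rule decides what the trial may claim, it should be fixed before unblinding.

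**What to change.** **Preferred.** Name EPDS change from T0 to T2 as the single primary outcome. It is the scale that section 2.4 describes as designed for perinatal populations, and it defines eligibility in 2.2. State in 2.9 that the 5% and 80% refer to it. Test PHQ-9 and then GAD-7 at T2 in fixed sequence, each at two-sided 5% and only if the preceding test succeeds.

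**Alternative.** Keep all three as primary, declare an any-of-three rule with Holm or Bonferroni, and restate the power in 2.9: about 80% or more for at least one success at correlations up to 0.8 (76% at 0.9), but about 66% for any single scale at 0.05/3.

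**Cost.** The sample size stays at 290 under either option. The abstract, the aims in the Introduction, 2.7, 2.9 and 2.10 must change together, or the new rule will contradict the remaining text. According to 2.1 recruitment began in November 2024, so the change alters the outcome definition during the trial. It should be made before unblinding and reported as a dated protocol amendment. Under the fixed sequence, a result on PHQ-9 or GAD-7 alone can no longer carry a positive claim; under the alternative, each scale faces a stricter threshold.

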### Statistical analysis

2.10

We will descriptively summarize participants’ baseline characteristics, outcome variables, satisfaction levels and adverse events. Independent t-tests or Mann-Whitney U tests will be performed to compare continuous variables, and chi-square or Fisher’s exact tests will be applied for categorical characteristics. To account for the correlation of repeated measures from the same participant, generalized linear models with random effects (participants) will be fitted to evaluate the intervention effect on outcome variables over time, adjusting for potential confounders such as age, parity, and family history of mental disorders.

Outcome analyses will be conducted on both the intention-to-treat population, which includes all randomized participants, and the per-protocol population, consisting of eligible participants who adhere to the planned intervention and follow ups. Missing data for primary and secondary outcomes will be imputed using the last value carried forward method in the intention-to-treat analysis. Additionally, to assess the impact of intervention adherence, adherence metrics—such as daily task completion rates and module progression—will be incorporated into sensitivity analyses. Participants will be stratified based on their engagement levels, and adherence data will be included as exploratory covariates in the regression models. These analyses will help determine whether engagement level influences intervention effectiveness and whether adherence plays a moderating role in treatment outcomes.

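### The only stated between-arm comparison of adverse events is at T1, so about two thirds of follow-up, including term birth and the postpartum period, has no stated comparison by arm

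*Protocol article*

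**What the plan says.** All references are to the protocol article.

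- **2.7 Outcomes.** The primary outcomes are changes in EPDS, PHQ-9 and GAD-7 from T0 to T2. Secondary outcome (ii) compares the CSQ-8 and "the number of adverse events post-intervention (T_1_) between the intervention and control groups".
- **2.4 Data collection and measurements.** On adverse events, "all reported events will be documented and monitored throughout the study period". The trial manager prepares "a report detailing the number of adverse event notifications at each assessment period for review by the safety board". No comparison by arm is mentioned there. Table 1 puts T1 at 8 weeks and T2 at 6 weeks postpartum; it has no row for adverse events.
- **2.10 Statistical analysis.** The descriptive summary covers baseline characteristics together with "outcome variables, satisfaction levels and adverse events". No time point is given for the adverse events.
- **2.1 Study design and setting.** Women enter "between 20 and 24 weeks of gestation".
- **3 Discussion.** Follow-up is said to stop at six weeks postpartum.

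**The concern.** The plan names a time point for its comparison of harms, and that time point is earlier than the one for its main efficacy claim. This is a choice the article states, not a detail left to an analysis plan. The main objective is postnatal depression, with the primary outcomes taken at T2. Harms are compared between arms only at the end of the 8-week programme, before any term birth.

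Followed as written, the report could state that adverse events did not differ between arms on about a third of follow-up, next to an efficacy result covering all of it. Two kinds of event would fall outside both the stated harm comparison and the T2 scales: physical events after T1, and distress that arises after T1 and resolves before T2. If a by-arm result for that period is added only after the data have been seen, it will carry less weight than one stated now.

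**Working it through.** The article gives no figure for the share of follow-up that the adverse event comparison covers, so there is none to reproduce. The check is one of dates.

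**Inputs**

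- Gestation at entry, g: 20 to 24 weeks (2.1).
- T1: 8 weeks after T0 (Table 1).
- T2: 6 weeks after birth (Table 1), the last assessment.
- Gestation at birth, b: not in the article. Assumed 40 weeks, with a range of 37 to 42.

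**Formulas**

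- Gestation at T1 = g + 8
- Total follow-up T0-T2 = (b − g) + 6 weeks
- Share after T1 = (total − 8) / total

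**Position of T1.** 20 + 8 = 28 and 24 + 8 = 32 weeks. A birth at 37 weeks or later therefore falls after T1, and so does the postpartum period that follows it.

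**Share of follow-up after T1**

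| Entry (weeks) | Birth (weeks, assumed) | T0-T2 (weeks) | T1-T2 (weeks) | Share after T1 |
|---|---|---|---|---|
| 20 | 37 | 23 | 15 | 65% |
| 20 | 40 | 26 | 18 | 69% |
| 20 | 42 | 28 | 20 | 71% |
| 24 | 37 | 19 | 11 | 58% |
| 24 | 40 | 22 | 14 | 64% |
| 24 | 42 | 24 | 16 | 67% |

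With birth at 40 weeks the stated comparison covers 8/26 = 31% to 8/22 = 36% of follow-up. The part left out is 64% to 69%, or 58% to 71% over the whole range of births.

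**Are events after T1 recorded?** The article does not say in so many words that adverse events are collected to 6 weeks postpartum. It follows from three statements taken together: recording runs for the whole study, counts are reported for each assessment period, and T2 is the last assessment.

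**Is there a by-arm comparison elsewhere?** Three places mention what is done with adverse event data. Section 2.7 compares arms, at T1. Section 2.4 reports counts to the safety board without mentioning arms. Section 2.10 summarises them descriptively, with no time point. None states a by-arm comparison for T1-T2 or T0-T2.

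**The case against.** The strongest defence is that T1 is a recognisable choice. Both programmes last 8 weeks and T1 closes that period, so the comparison at T1 is an on-programme one. Section 2.4 gives experiences related to the intervention among its examples of events, and the one specific hazard the article addresses is discomfort during breathing exercises. Later events still reach a safety board that can recommend stopping the trial. A descriptive table to T2 would be compatible with 2.10, and fuller tabulation may sit in an analysis plan that is not shown. Lasting distress would also show in the EPDS, PHQ-9 and GAD-7 at T2, which are compared between arms. All of this stands. It lowers the severity and is a reason to keep the T1 comparison. It does not supply a stated comparison by arm for the later period.

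A reader might infer more from the text than it supports:

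- **That exposure runs past week 8.** Section 2.5 says "If the user misses a daily challenge, she can complete that challenge in the later days". The later days may all lie within the 8 weeks; the sentence does not establish use after T1.
- **That the planned tests mishandle women with several events.** Section 2.10 assigns chi-square and Fisher tests to categorical characteristics and does not say which test applies to the adverse event count. A count per woman compared by a Mann-Whitney test would keep the woman as the unit.
- **That stopping at T1 must cost power.** The answer depends on when the excess occurs. Take 145 women per arm, a two-sided 5% Fisher test and assumed risks of 5% v 15%. If those risks apply by T2 with a constant hazard in each arm, power is 78% with events to T2 and 23% to 29% with events to T1. If they apply by T1, with no excess afterwards and an equal background risk of 10% or 20% in both arms after T1, power is 78% to T1 and 44% or 28% to T2. The article does not say which pattern to expect, so neither result shows a defect.

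**Conclusion.** The point holds in a limited form. The only by-arm comparison of adverse events that the article states is at T1. The remaining 64% to 69% of follow-up (birth at 40 weeks, assumed; 58% to 71% for 37 to 42 weeks) has none, and it contains term birth and the postpartum period. The result rests on the assumed gestation at birth and on reading the recording rule in 2.4 as running to T2.

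A reader might go further and conclude that late harms are ignored, or that T1 is the wrong time point. The documents do not support either conclusion: later events are recorded and monitored, and an on-programme comparison is useful in itself. The gap is a missing second period, not a wrong first one. No effect on the primary analysis follows. Severity is minor.

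**What to change.** In 2.7, keep the adverse event comparison for T0-T1 and describe it as the on-programme comparison. Add a sentence that, for T1-T2 and for T0-T2, the number and proportion of women with at least one adverse event, and with at least one serious adverse event, will be given by arm with a 95% confidence interval for the difference. Leave the CSQ-8 at T1.

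The cost is one sentence and one table, and no new data. The downside is small: obstetric background events after T1 can dilute a difference that arose during the programme. For that reason the longer period should be added to the T1 comparison rather than replace it, and the two periods should be shown separately.
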